## Abstract

**Background:**

Chronic gastritis (CG), a poorly understood entity, is a very common disease of the digestive tract and is difficult to cure. Chronic non-atrophic gastritis (CNG) is the most common type of CG. Even if treated with current standard chemotherapy, some patients will not be freed from this confusing disease. Many studies have shown traditional Chinese medicine (TCM) is more effective compared to chemotherapy in the treatment of chronic gastritis and no serious side effects have been identified. However, the studies that have been carried out were not scientifically rigorous trials. Our aim is to design a high-quality trial for a new TCM drug, the Jian-Wei-Qu-Tong Pills (JWQTP), to investigate the efficacy and safety of this new drug in treating chronic non-atrophic gastritis patients with spleen and stomach qi deficiency with damp-heat stasis syndrome (SSQDDSS).

**Methods/Design:**

This is a phase II, multicenter, parallel-group, double-blind, randomized and placebo-controlled trial. A total of 240 participants will be assigned to a high-dose group, a low-dose group or a placebo control group with a 1:1:1 ratio at five sites. Then, one dose (six 1-g pills), with a variable ratio between real drug and dummy drug according to the intervention protocol, will be taken three times a day before each meal for 8 weeks. The primary outcome is the eradication rate of epigastric pain. The secondary outcome includes the changes of endoscopic examination, histopathological examination, traditional Chinese medicine symptom scores and patient-reported outcome instrument scores for chronic gastrointestinal diseases and the eradication rate of *Helicobacter pylori* (HP).

**Discussion:**

Many CNG patients suffer from frequent, recurrent bouts of dyspeptic symptoms. This is the first clinical trial to evaluate the safety and efficacy of JWQTP in treating CNG with SSQDDSS in a multicenter, parallel-group, double-blind, randomized and placebo-controlled manner. This trial may not only provide evidence for a phase III clinical trial, but also a vision of an alternative option for CNG treatment.

**Trial registration:**

The registration number, ChiCTR-TRC-14004088, was assigned by the Chinese Clinical Trial Registry on 7 January 2014.

## Background

Chronic gastritis (CG), which is induced by various causes, is a very common disease of the digestive tract and is an inflammatory condition of the gastric mucosa [1]. Among the possible etiological factors, *Helicobacter pylori* (HP) infection is the most common cause of chronic gastritis worldwide, with the remaining cases arising due to smoking, drinking, duodenal juice reflux, food allergies, heredity, drug-induced injuries, immunity, Crohn’s disease, other infectious pathogens or radiation [2-4]. Chronic gastritis can be categorized into non-atrophic gastritis, atrophic gastritis and special types of gastritis, according to the Consensus on Chronic Gastritis in China (Shanghai 2012) [5]. Chronic non-atrophic gastritis (CNG) is characterized by the infiltration of chronic inflammatory cells and the absence of atrophy in the mucosal layer. Although the prevalence rate in the general population remains unclear, a national multicenter cross-sectional study led by the Digestive Endoscopy Branch of Chinese Medical Association showed that 49.3% of the investigated patients (4,389/8,892) with upper gastrointestinal symptoms who underwent diagnostic upper endoscopy for the evaluation of gastrointestinal symptoms from 33 centers had CNG, which was the most common [6]. Symptomatic patients with CNG may manifest nonspecific dyspeptic symptoms, such as epigastric discomfort, distention, belching, acid regurgitation, nausea, vomiting, loss of appetite and anergy, while some patients have no symptoms. The pathogenesis of chronic gastritis is complex and difficult to cure. The focused Western medical treatment of chronic gastritis involves the eradication of HP, antacids, prokinetics and mucosal-protective agents to ameliorate the symptoms [5,6]. However, even if treated with the above standard therapies, some patients will not be freed from this disease. Traditional Chinese medicine (TCM), which has recently become a research focus in particular contexts, can broaden the therapeutic approaches to CNG [7-11].

Traditional Chinese medicine, which has been established for over 5,000 years, has been widely used to treat diseases, including CNG. Based on its clinical manifestations, CNG can be categorized as Weiwantong (stomach ache), Piman (abdominal distention) or Caoza (gastritis discomfort) in the field of Chinese medicine (CM); TCM divides CNG into five common single syndrome patterns: (1) spleen (Pi) and stomach (Wei) deficiency syndrome (including spleen and stomach qi deficiency syndrome and spleen and stomach deficiency-cold syndrome); (2) incoordination between liver (Gan) and stomach syndrome (including liver qi invading stomach syndrome and stagnant heat in liver and stomach syndrome); (3) stomach yin deficiency syndrome; (4) spleen and stomach dampness-heat syndrome; and (5) blood stasis in stomach collaterals syndrome [3]. The concurrence of two or more individual patterns can be considered a complicated pattern and is common in clinical practice [12]. The TCM treatment relies on correct syndrome differentiation (SD), by which accumulating symptoms and signs are identified through inspection, auscultation and olfaction, inquiring, and palpation to uncover the ongoing abnormal condition. Therefore, TCM agents operate through other pathways that may be helpful for patients who are nonresponsive to standard therapies.

A new TCM drug, the Jian-Wei-Qu-Tong Pills (JWQTP), is currently being manufactured by Anbang Pharmaceutical Limited by Share Ltd, Hunan, China. The prescription for this pill is based on both TCM theory and the clinical experience and herbal studies of prominent TCM doctors on the treatment of CNG. Components of the pill include: Radix Pseudostellariae, Rhizoma Coptidis, Rhizoma Atractylodis Macrocephalae, Semen Coicis, Rhizoma Pinelliae Preparata, Radix Notoginseng, Pollen Typhae, Herba Taraxaci Mongolici, Rhizoma Corydalis Yanhusuo, Cortex Magnoliae Officinalis and Radix Glycyrrhizae preparata. All of these herbs have been approved by the China Food and Drug Administration (CFDA). This pill can strengthen the spleen, supplement qi, clear heat, remove dampness and promote blood circulation to remove blood stasis and relieve pain. Thus, it can be used for spleen and stomach qi deficiency with damp-heat stasis syndrome (SSQDDSS) in CNG patients. Preclinical pharmacologic experiments, which have not been published, show that JWQTP can neutralize gastric acid; reduce gastric acidity, pepsin activity, free mucus, gastrin, TNF-α and IL-2; elevate the level of IL-4; create balance between the Th1 and Th2 cells; and then reduce inflammation in rats’ gastric mucosa to protect against CG. Furthermore, this treatment was able to eradicate HP in the gastric mucosa of mice to some degree, provide an analgesic effect and play a regulatory role on gastric emptying. Additionally, there was no evidence to show an adverse or toxic effect in toxicological studies.

The specific objectives of this trial included evaluating the efficacy and safety of JWQTP in treating CNG patients with SSQDDSS, including any dose-effect relationship, and providing evidence for a Phase III clinical program.

## Methods/Design

This current study is a phase II, multicenter, parallel-group, double-blind, randomized and placebo-controlled trial. The study will be conducted in compliance with the Declaration of Helsinki, Good Clinical Practice (GCP) Guidelines [13] and the requirements of clinical trials by the Drug Administration Law of the People's Republic of China, and will strictly observe all laws governing new TCM drugs. The study was approved by the CFDA (Approval No. 2012 L02382), and the protocol and informed consent were reviewed and approved by the West China Hospital of Sichuan University Clinical Trials and Biomedical Ethics Committee (No. TCM-2013-06). In addition, it was registered in the Chinese Clinical Trial Registry (ChiCTR-TRC-14004088). We will recruit subjects by advertising on the hospital’s notice board or through recommendations in the outpatient clinic. All patients must provide written informed consent. The trial is financially supported by Anbang Pharmaceutical Limited by Share Ltd, Hunan, China, which did not contribute to the study design, data collection, data management, analysis, interpretation of data or decision to submit the report for publication, except for the provision of all test drugs. Each trial center has a project manager who is responsible for the quality of research. Standard training will be required for all investigators before the trial. An independent trial inspector will pay regular visits to each center, check the case report forms (CRFs) and supervise the research to make sure it complies with the protocol throughout the trial. Figure 1 shows the flow chart of this trial.

**Figure 1 F1:**
[figure not shown]
Study flow chart.

### Patient population and setting

A total of 240 patients will be enrolled at the following five sites: (1) West China Hospital of Sichuan University, (2) the first Affiliated Hospital of Guiyang College of Traditional Chinese medicine, (3) the first Affiliated Hospital of Hunan University of Chinese Medicine, (4) the first Affiliated Hospital of Guangxi University of Chinese Medicine and (5) the Ruikang Hospital affiliated to Guangxi University of Chinese Medicine. In other words, 48 patients will be recruited at each hospital.

### Randomization

For randomization, the participants will be assigned into a high-dose group, a low-dose group or a placebo control group, with a 1:1:1 ratio using a stratified randomization method, with stratification by center. The randomization sequence will be created at the West China Hospital of Sichuan using SAS 9.2 software to determine the appropriate segment. Two copies of the randomization list will be kept in safe places - one by the West China Hospital of Sichuan University drug clinical trial agency and one by the sponsor of this study - during the study period. Each patient will receive a unique randomized test number corresponding to the specified drug, according to the group allocation. An emergency envelope has been prepared for each test number and is to be opened for treatment allocation only due to medical emergency.

### Diagnosis in Western medicine

Referring to consensus on chronic gastritis in China (Shanghai, 2012) [5], consensus on the diagnosis and treatment of chronic gastritis by integrative medicine (Tianjin 2011) [14], Practice of Internal Medicine (2009, Version 13) [15] and endoscopic classification and trial standards on treatment of chronic gastritis (Dalian, 2003) [16], which is the diagnostic criteria for CNG in Western medicine, are listed as follows:

#### Clinical manifestations

Most symptomatic patients with CNG have nonspecific dyspepsia, such as epigastric pain, distention, belching, acid regurgitation, nausea, vomiting and loss of appetite.

#### Physical signs

There is no finding in most patients’ physical examinations, although some patients may feel slight epigastric pain or discomfort when pressed on the upper abdomen. Only a tiny minority of these patients are gaunt or anemic.

#### Endoscopic and histopathological diagnosis

Because there is no specific symptom, the diagnosis of CNG relies primarily on endoscopic and histopathological examinations, particularly the latter. The fundamental appearance of non-atrophic gastritis shows red plaques (punctuates, patches and striae), coarse and uneven mucosa, hemorrhagic spots/plaques, edematous mucosa, and exudates at endoscopy. No atrophic changes, intestinal metaplasia, dysplasia or pseudopyloric gland metaplasia are found in the histopathological examination of the gastric mucosa. Table 1 shows that the red plaques, erosion, hemorrhage and bile reflux are further graded into four grades at endoscopy, as chronic inflammation and active chronic inflammation in the histopathological examination observed are in Table 2.

**Table 1 T1:** Endoscopic characteristics, grading and scoring

**Endoscopic appearance**	**Endoscopic characteristics**	**Grading system**	**Score**
**Red plaques**	Apparent rubefaction in the normal gastric mucosa	None	0
		Grade I: sporadic or interrupted linear type	1
		Grade II: intensive plaques or linear series type	2
		Grade III: extensive fusion	3
**Erosion**	Flattened or varioliform erosions: superficial mucosa is ruptured, along with flat or ridged erosion in the surrounding area	None	0
		Grade I: sporadic	1
		Grade II: local, multiple but no more than five	2
		Grade III: extensive, multiple and no less than six	3
**Hemorrhage**	Hemorrhage in the mucosa: flattened hemorrhagic spots/plaques with bright red or dark red, together or not with errhysis	None	0
		Grade I: local	1
		Grade II: multiple sites	2
		Grade III: widespread	3
**Bile reflux**	Olive green gastric juice; bile flow back into stomach because of opened pyloric orifice	None	0
		Grade I: yellowish or flavo-green mucinous lake	1
		Grade II: lies between grade I and grade III	2
		Grade III: massive yellow bile flow back into stomach, yellow mucus adhere to gastric mucosa	3

**Table 2 T2:** **Histopathological changes, grading and scoring**^
**a**
^

**Histopathological changes**	**Grading system**	**Score**
**Chronic inflammation**	Normal or number of mononuclear cells less than 5/high power field	0
	+ (mild): Some chronic inflammatory cells are localized in the superficial layer of the mucosa, but not more than 1/3 of the depth of the mucosa;	1
	++ (moderate): A more dense accumulation of chronic inflammatory cells, but not exceeding 2/3 of the depth of the mucosa	2
	+++ (severe): A dense accumulation of chronic inflammatory cells occupying the whole depth of the mucosa	3
**Active chronic inflammation**	Normal	0
	+ (mile): Few neutrophils in the lamina propria of the mucosa	1
	++ (moderate): More neutrophils in the mucosal layer and between superficial epithelial cells, pit epithelial cells and glandular epithelial cells.	2
	+++ (severe): A more dense infiltration of neutrophils, or abscess on pits can be seen in addition to what is seen in moderate activity.	3

^**a**^Two to five biopsy specimens reaching musculature in the mucosa will be taken from gastric antral, gastric angle or suspected focal lesions of sufficient size. For the specimens taken at the first and sixth visits, the regions should be chosen consistently as possible as it can.

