### Inclusion criteria

Inclusion criteria are:

1. Diagnosis of CNG according to Western medicine (moderate or severe level of chronic inflammation and/or active inflammation).

2. Diagnosis of spleen and stomach qi deficiency with damp-heat stasis syndrome, according to TCM syndrome differentiation.

3. Aged between 18 and 65 years.

4. Voluntary provision of written informed consent prior to enrollment.

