#### Secondary outcomes

##### Endoscopic and histopathological examination

The change in red plaques, hemorrhagic spots/plaques, erosion and bile reflux at endoscopy and the grade of active chronic inflammation and chronic inflammation in the gastric mucosa, depending on the histopathological examination of biopsy specimens, will be compared between visits one and six, according to the consensus on CG in China.

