An analysis of variance (ANOVA) or chi-square test will be used to compare baselines among patients, including demographic data, vital signs, history of diseases, basic treatment and so on. For the comparison of variations from the baseline to endpoint, Student’s t-test will be performed on variables with normal distributions, and the Wilcoxon rank sum test will be performed on variables with non-normal distributions. The evaluation of therapeutic effects will primarily be performed between baseline and visit six, in compliance with PPS, or the time to withdraw from the study, in compliance with FAS. In addition, the changes from baseline to visits two, three, four or five will be evaluated. For continuous variables regarding therapeutic effect, an ANOVA will be used for multiple comparisons of variation from baseline among different groups, and Dunnett’s tests will be used for comparisons within a group. A covariance analysis, adjusted for the baseline covariate, will be used to evaluate the differences of the symptom scores, VAS scores and PRO instrument scores among the groups considering the center effect. The least square mean in each group and the 95% confidence intervals of mean differences among groups will be calculated. The Cochran-Mantel-Haenszel test, stratified by center effect, and the logistic regression model, adjusted for covariates, will be used on categorical variables in addition to the chi-square test, Wilcoxon rank sum test or Fisher’s exact test. The total drop-out rate in each group will be compared with the drop-out rate due to AEs for drop-out analyses using chi-square test or Fisher’s exact test. For safety analyses, we will perform the chi-square test or Fisher’s exact test to evaluate the incidence rate of AEs among the groups and describe AEs using descriptive statistics through listing.

All statistical tests will be performed by an independent statistician using SAS 9.2, assuming a two-sided test and a 0.05 level of significance.

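### Visit-one histology is both entry gate and baseline, so a within-arm fall by visit six is expected with no drug effect; compare the grades between arms, adjusted for the visit-one grade

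*Protocol article*

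**What the plan says.** All references are to the protocol article.

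- **Inclusion criteria, item 1:** entry requires a "moderate or severe level of chronic inflammation and/or active inflammation". On the Table 2 scales that is grade 2 or 3 on at least one of the two.
- **Table 2 footnote:** "Two to five biopsy specimens reaching musculature in the mucosa will be taken from gastric antral, gastric angle or suspected focal lesions". It continues: "For the specimens taken at the first and sixth visits, the regions should be chosen consistently as possible as it can". Regions therefore have a soft matching rule. The number of specimens has none, and the article does not say how several specimens yield one grade.
- **Secondary outcomes, Endoscopic and histopathological examination:** the endoscopic changes and the two inflammation grades "will be compared between visits one and six, according to the consensus on CG in China".
- **Statistical analysis:** a baseline-adjusted covariance analysis that considers centre "will be used to evaluate the differences of the symptom scores, VAS scores and PRO instrument scores among the groups". Histology and endoscopy are not in that list. For categorical variables the section plans a Cochran-Mantel-Haenszel test stratified by centre and a covariate-adjusted logistic model, besides chi-square, Wilcoxon rank sum and Fisher tests. It also evaluates therapeutic effect mainly from baseline to visit six and gives Dunnett's tests for comparisons within a group.
- **Abstract, Methods/Design:** "A total of 240 participants will be assigned to a high-dose group, a low-dose group or a placebo control group with a 1:1:1 ratio", double-blind.

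**The concern.** The visit-one biopsy does two jobs: it decides who enters and it supplies the baseline. A patient whose specimens happen to read high is more likely to be admitted, and the second reading will on average lie nearer that patient's usual level. Grades then fall by visit six in all three arms, placebo included, whatever the drug does.

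This would not matter if the outcome were plainly a contrast between arms. The outcome section instead defines it by visit, and the one analysis said to adjust for baseline leaves it out. That makes it easy to report a fall within the JWQTP arms as a mucosal effect. The trial is meant to inform dose and a phase III programme (Background, Discussion), and the Discussion names reduced mucosal inflammation as a therapeutic aim. The Discussion also says that symptoms and histology are not clearly correlated, so the symptom results could not be relied on to expose a spurious histological fall.

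Varying the number and region of specimens between visits adds measurement noise to the same outcome.

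**Working it through.** **The plan's own figure.** The article gives no figure for histology. Its one design figure, 66 per group for 55% v 30%, reproduces with unpooled variance, two-sided α = 0.05 and power 0.85: (1.960 + 1.036)² × (0.55 × 0.45 + 0.30 × 0.70) / 0.25² = 8.98 × 0.4575 / 0.0625 ≈ 65.7, so 66. This point does not depend on it. It is mentioned because 240 / 3 = 80 per arm is used below.

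**Inputs from the article.** Grades 0 to 3; entry at grade 2 or more; 2 to 5 specimens at each visit; 80 patients per arm.

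**Assumptions, because the article gives no biopsy variability.** Latent severity has mean 1.5 and SD 0.9, cut at 0.5, 1.5 and 2.5 into grades 0 to 3. The between-patient share of variance (ICC) is 0.4, 0.6 or 0.8. The worst specimen sets the grade. Drug effect is zero. One scale is modelled.

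**Step 1: mean change in grade, visit one to visit six, among patients admitted**

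| ICC | Random 2-5 at each visit | 5 and 5 | 2 and 2 | 5 then 2 | 2 then 5 |
|---|---|---|---|---|---|
| 0.4 | -0.17 | -0.10 | -0.26 | -0.48 | +0.11 |
| 0.6 | -0.15 | -0.10 | -0.21 | -0.41 | +0.10 |
| 0.8 | -0.11 | -0.09 | -0.14 | -0.31 | +0.07 |

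In the random 2-5 column, 30%, 26% and 20% of patients have a lower grade at visit six, against 16%, 13% and 9% with a higher one. A fall remains with five specimens at both visits, so selection at entry produces it even when sampling is constant. If the grade is the mean of the specimens (entry at a mean of 1.5 or more), the random 2-5 fall is 0.18 to 0.07.

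**Step 2: what this does to tests.** Two arms of 80, random 2-5 specimens, no drug effect, 1,500 simulated trials for each ICC:

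- one-sample t-test of change within an arm: rejects in 46% to 55% of trials;
- Wilcoxon rank sum test of change between arms: rejects in 4% to 5%, with a mean difference of about 0.

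**Step 3: what the two changes gain.** Same model, random 2-5 specimens, worst specimen graded.

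- *Adjusting for the visit-one grade instead of using the change score.* Residual variance goes from 0.516 to 0.441 (ICC 0.4), 0.413 to 0.377 (0.6) and 0.289 to 0.276 (0.8). The reductions are 1 - 0.441/0.516 = 15%, 1 - 0.377/0.413 = 9% and 1 - 0.276/0.289 ≈ 5%.
- *Repeating each patient's own number of specimens at visit six.* Variance of the change goes from 0.516 to 0.489, 0.413 to 0.394 and 0.289 to 0.277, a reduction of 4% to 5%. The mean fall hardly moves (0.16, 0.14 and 0.11), so matching removes noise and does not cure regression to the mean.

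**The case against.** The strongest reply is that the placebo arm exists for this purpose. Selection and sampling noise fall alike on three randomised, blinded arms, so drug against placebo stays unbiased. That stands, and Step 2 confirms it. A reader might infer from the selection and the loose sampling that the histology comparison with placebo is biased; the documents do not support that.

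Second, the Statistical analysis section already provides between-arm methods for categorical variables, stratified by centre or adjusted for covariates, and naming covariates is usually left to an analysis plan that is not shown. This stands in large part. Suitable methods are available, and nowhere does the article say that a within-arm fall will count as efficacy. What remains is that the outcome is worded by visit and that the baseline-adjusted analysis lists other outcomes, without tying any method or the visit-one grade to histology.

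Third, a reader might infer that the 2-5 range itself pushes grades down, for instance by supposing five specimens at visit one and two at visit six for everyone. That is one extreme under a worst-specimen rule the article does not state. The reverse order raises the grade (Step 1), and nothing suggests a systematic drop in number. A reader might likewise want only two fixed specimens scored. In the same model that enlarges the null fall to 0.14 to 0.26.

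Fourth, region is not left open: the footnote asks for consistency, if softly. Fifth, the and/or in the entry criterion means that a patient may qualify on one scale only, so regression on the other scale may be weaker. Both points stand. Entry sets no endoscopic grade threshold either, so the selection argument is about histology; endoscopy shares only the wording and the missing adjustment.

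**Conclusion.** The point holds in a limited form. Because the same biopsies gate entry and form the baseline, histology grades can be expected to fall from visit one to visit six in every arm with no drug effect. The fall is about 0.11 to 0.17 grade under the assumed variability with 2 to 5 specimens at random. A within-arm fall should not be read as efficacy; under those assumptions a within-arm test would be significant in roughly half of null trials.

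The comparison with placebo keeps its error rate. The unmatched specimen number and soft region rule cost it some precision, and adjustment for the visit-one grade recovers about 5% to 15% of residual variance relative to a change score. All these sizes rest on assumed biopsy variability and an assumed grading rule. The direction of the within-arm fall needs only selection on an imperfectly repeatable reading. It concerns secondary outcomes only; epigastric pain, the primary outcome, is unaffected.

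**What to change.** 1. **Secondary outcomes and Statistical analysis.** State the histology and endoscopy outcomes as the visit-six grade compared between each JWQTP arm and placebo, adjusted for the visit-one grade and stratified by centre, for example with an ordinal model. State that change within an arm is descriptive only.
2. **Table 2 footnote.** Require visit six to repeat each patient's own visit-one number of specimens and regions, within the planned two to five. Record number and region at both visits, so that any departure is visible.

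The cost is wording and slightly more record-keeping at the sites. The planned range of specimens is unchanged, and the visit-one grade is already collected. The Trial status section says the trial was still preparing to recruit, so both changes could be made before the first patient.
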